## Abstract

**Background:**

Suicide attempts (SA) constitute a serious clinical problem. People who attempt suicide are at high risk of further repetition. However, no interventions have been shown to be effective in reducing repetition in this group of patients.

**Methods/Design:**

Multicentre randomized controlled trial.

We examine the effectiveness of «ALGOS algorithm»: an intervention based in a decisional tree of contact type which aims at reducing the incidence of repeated suicide attempt during 6 months. This algorithm of case management comprises the two strategies of intervention that showed a significant reduction in the number of SA repeaters: systematic telephone contact (ineffective in first-attempters) and «Crisis card» (effective only in first-attempters). Participants who are lost from contact and those refusing healthcare, can then benefit from «short letters» or «postcards».

**Discussion:**

ALGOS algorithm is easily reproducible and inexpensive intervention that will supply the guidelines for assessment and management of a population sometimes in difficulties with healthcare compliance. Furthermore, it will target some of these subgroups of patients by providing specific interventions for optimizing the benefits of case management strategy.

**Trial Registration:**

The study was registered with the ClinicalTrials.gov Registry; number: NCT01123174.

## Background

Suicidal behaviors are multifactorial phenomena. It is therefore difficult to define only one strategy to manage a suicidal attempt (SA) for the whole population [1]. In a review of literature of the last 25 years, considering only randomized controlled trials (RCT) with suicidal repetition as primary endpoint, we only find 7 positive trials out of 24 studies. However, all studies show an improvement of compliance to the healthcare plan, which has led some to say that it doesn't matter what is suggested to suicide attempters, as long as they are offered something [2,3].

The seven positive trials can be divided into two categories: intensive intervention programs (nursing at home [4], and a series of Brief Psychotherapy Interventions (IPB) [5]) and, case management programs.

The strategies of intensive intervention demonstrate their effectiveness in reducing the number of SA repetitions at short and medium term, but their weakness lies in the institutional heaviness of deployment and their expensive financial costs.

The other case management strategies have one common point: they are distinct from classical interventions, by proposing a "stay in contact" program, which does not invade the daily life of suicidal attempter, and can be employed in parallel to the eventual healthcare and offers a reliable and effective treatment in cases of suicidal crisis. This kind of case management has inspired the pioneer Jerome Motto about the neologism of "connectedness" [6].

Each one of these strategies is of a great interest in certain categories of suicide attempters. They differ from the first two ones by having not only a lower financial cost but also an easier set up for the entire population in a given territory.

In the "SYSCALL" study, 605 suicidal patients discharged directly from Emergency Departments (ED) were included [7]. A specially trained psychologist contacted patients by telephone, one or three months after the SA. The aim of this psychological supportive intervention was to evaluate the success of the treatment plan defined during the ED stay and eventually adjust it. Over the 13 months follow-up, there were 150 participants who reattempted suicide, 48 of them before the one month' telephone contact. Considering only the subjects effectively contacted (per protocol analysis), the telephone contact at one month proved to be very effective, by reducing to about the half the number of suicidal reattempts over one year (12% versus 21.6% in the control group). The post-hoc analysis showed no effect of the contact in first-attempters. The proposal of telephone contact was very well accepted and positively perceived by the population of this study. In addition, no major side effects were reported by the participants [8].

The strategy based on the delivery of a "crisis card" was proposed by the English team of Bristol and was especially interesting for first-attempters. In addition to usual treatment, the intervention group was offered a "resource card" with the telephone number of a junior doctor in psychiatry available 24 hours a day. The intervention had a significant effect on the rate of SA repetition at 6 months in the first attempters subgroup only, compared to a control group (odds ratio 0.64, 95% CI 0.34-1.26) [9]. The beneficial effect observed at 6 months was not maintained at one year [10].

Jerome Motto proposed the strategy of sending letters to maintain contact with patients at high risk of suicide, who refused to remain in the healthcare system. Patients were contacted by short letters, sent by a person who met them during their hospital stay. The letters were personalized whenever possible. A self-addressed, unstamped envelope was always enclosed. These letters were sent monthly for four months, then every two months for eight months, and finally every three months for four years (24 letters in total). The objective was to make the patient realize that there is a person concerned about him (its existence), and who maintains positive feelings towards him, hence the neologism of "connectedness" proposed by the author. This study included 3.005 patients admitted to hospital for a depression or a suicidal crisis in San Francisco from 1969 to 1974. Thirty days after hospital discharge, subjects were questioned by telephone about adherence to the defined therapy plan; non-compliant subjects were then randomized into two parallel groups with (N = 389) or without sending letters (N = 454). The primary endpoint of the study was to evaluate the impact on suicide rate. This study showed contrasted results at 5 and 15 years. Patients in the contact group had a lower suicide rate at five years (15/389 vs 21/454). Formal survival analyses revealed a significantly lower rate in the contact group (p = .04) for the first two years; differences in the rates gradually diminished, and by year 14 no differences between groups were observed (25/389 vs 26/454) [11].

Like Motto's intervention, an Australian study tested the effectiveness of a programmed systematic sending of a postcard (postcards from the EDge project) during the year following the SA [12]. The intervention consisted of a postcard sent to participants in a sealed envelope at 1, 2, 3, 4, 6, 8, 10, and 12 months after discharge (a total of 8 postcards). The message was the same for all postcards: «*It has been a short time since you were here at the hospital, and we hope things are going well for you... if you wish to drop us a note, we would be happy to hear from you»*. The evaluation concerned all deliberate self poisoning patients admitted for few days in a toxicology unit. The initial follow-up was for 12 months, completed later with a one-year extension [13]. The proportion of SA repeaters in the intervention group did not differ significantly from that in the control group (15.1% vs. 17.3% at one year, 21.2% vs. 22.8% at two years). However, among SA repeaters there was a lower number of reattempts in contact group (incidence risk ratio 0.55 at one year, and 0.49 at two years).

These findings were recently replicated by the New Zealand team of Beautrais: 327 suicide attempters aged 16 years or older, presenting consecutively to ED were included [14]. The intervention consisted of sending four "postcards" to participants at two weeks, 1, 3 and 6 months. Patients allocated to control group did not receive any postcards. All subjects received a standard treatment in parallel. The number of SA repeaters was significantly lower in intervention group (31/153, 20.3%) than in control group (88/174, 50.6%).

Thus, by taking into consideration the strengths and limitations of each of these four strategies, we propose to construct a decisional tree of contact type, a case management algorithm. This monitoring algorithm entitled «ALGOS» is based on the two interventions that showed a significant reduction in the number of SA repeaters: systematic telephone contact (ineffective in first-attempters) and «crisis card» (effective only in first-attempters). Participants non contacted during phone call periods and those refusing proposed healthcare, can then benefit from the «short letters» of Motto or the «postcards» of Carter.

## Aims and Hypothesis

The hypothesis is that deployment of «ALGOS» algorithm following a SA, in parallel to usual treatment; will contribute to the reduction of suicidal behaviours at the six months follow-up. ALGOS algorithm would be more a «crisis management plan», rather than a «case management plan».

The main objective is to evaluate the effectiveness of the algorithm in reducing the number of SA repeaters during a six months period, compared to a control group of suicide attempters benefiting from usual treatment.

Secondary objectives to be studied are:

- Evaluating, according to the method validated by Beecham in 1992 [15], the medical and economic impact within the year following the introduction of ALGOS algorithm

- Evaluating the reduction of other suicidal behaviours at 6 months (decrease of the total number of suicide re-attempts in each group, evolution of Beck's suicidal ideation score, etc ...)

- Assessing the maintenance of the algorithm is effectiveness on suicidal behaviour at 13 months

- Evaluating the differences in the delay of SA repetition within the two groups during the deployment of the algorithm at 6 months and 13 months

- Finally, a more qualitative assessment may propose different responding profiles according to the psychopathology spotted by MINI, the character of being first-attempters or not, sex, etc...

## Methods/Design

It is a multicentre, prospective, comparative, single-blind, randomized controlled trial (ClinicalTrials.gov; number: NCT01123174). It was authorized by AFSSAPS (French Health Ministry) and approved by the Northwest IV Ethical Committee for the Protection of Persons.

## Setting

23 national centres employing psychiatrists and emergency physicians, who are strongly implicated in the treatment of suicidal patients and benefiting from a close collaboration, participate in this program: CHU Angers, CHU Brest, CHU Caen, CHU Clermont Ferrand, CHU Créteil Henri Mondor, CHU Lille, CHU Marseille, CHU Montpellier, CHU Nancy, CHU Nantes, CHU Nice, CHU Paris HEGP, CHU Rennes, CHU Toulouse, CH Boulogne, CH Douai, CH Dunkerque, Polyclinics of Henin Beaumont, CH of Montauban, CH Quimper, CH Roubaix, CH Tourcoing, CH Vannes.

The deployment of the algorithm is supervised by the University Hospital of Lille and the evaluations are carried out by the Clinical Investigation Centre (CIC 9301). The research team has been practising these procedures of follow-up for more than 10 years (these telephone contacts), were realized as a part of previous studies, such as SA patients and road traffic accidents victims. These telephonic assessments are conducted by specially trained psychologists using validated landmarks.

## Participants

Inclusions can be done during the ED stay or at the discharge from hospital, within 7 days after SA. 900 subjects, men or women aged over 18 years, and surviving a SA, whatever the mode of SA is, will be included. Patients with 4 or more SA during the past three years (multi repeaters) will not be included.

The participants will give their free, informed, dated and signed consent.

## Randomisation

Once the patient is included, the investigator randomizes him into one of two groups, intervention (ALGOS) group or control group, using randomization envelopes. Hence the trial is single-blind, the investigator knows the allocated group but not the patient.

Randomization done by blocks is centralized at the CIC of Lille, who follows the inclusions and their distribution in each group. If asymmetrical distribution appears after an intermediate observation of the first 450 inclusions, it will be possible to make rebalance between groups, by a person exterior to the study, according to the number of SA.

## Procedure

After verification of inclusion criteria, a physician informs and answers any questions of the participant in order to get his «consent for a following contact». The participant is then randomized and allocated to ALGOS group or control group. The physician collects the following data: socio-demographic characteristics (including place of birth and place of residence), number of previous SA and headlines of the "care plan defined in ED" (presence or absence of a companion at hospital discharge, recommended psychiatric care, scheduled appointments, prescription of psychotropic drugs, etc ...).

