## Intervention

### For ALGOS patients group

#### 1. Delivery of a «Crisis Card»

All participants surviving a first SA receive a «crisis card» with the emergency phone numbers of the centre where they are included. This card is inspired from the proposed "crisis card" of Evans'team: format of a credit card, green (the colour of hope), plastified, identical for the whole territory containing the logos of suicide prevention organizations (with websites addresses) and personalized with the phone number of the 24 h care permanence of the concerned centre (see Figure 1) [10].

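### Attempt history and the ED care plan are described as recorded after randomisation, by staff who know the arm; record them before the envelope is opened

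*Protocol article*

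**What the plan says.** The Procedure section of the protocol article sets out the steps at inclusion. It opens with eligibility and information to the patient: "After verification of inclusion criteria, a physician informs and answers any questions of the participant". Consent follows, and then: "The participant is then randomized and allocated to ALGOS group or control group. The physician collects the following data: socio-demographic characteristics". The list of data goes on to "number of previous SA and headlines of the 'care plan defined in ED", with recommended psychiatric care, appointments and psychotropic prescriptions among its items.

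The Randomisation section says that "the investigator randomizes him into one of two groups, intervention (ALGOS) group or control group, using randomization envelopes", and describes the blinding as one in which "the investigator knows the allocated group but not the patient".

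Three other places bear on the point:

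- Participants section, on eligibility: "Patients with 4 or more SA during the past three years (multi repeaters) will not be included". The same section allows inclusion either during the ED stay or at hospital discharge, within 7 days of the attempt.
- Crisis card section, for the ALGOS arm: "All participants surviving a first SA receive a" crisis card. The Telephone contact section gives all other ALGOS patients a call between day 10 and day 21.
- Randomisation section: if the groups look unbalanced after the first 450 inclusions, they may be rebalanced by number of attempts.

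**The concern.** A baseline variable is safe to use for subgroups, adjustment or balance checks when it was fixed without knowledge of the arm. In the order described here, two items that matter are recorded when the person recording them may already know the allocation.

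The first is attempt history. In the ALGOS arm it decides which component the patient receives. In the control arm nothing depends on it. A physician who knows the arm therefore has a reason to resolve an uncertain history one way in one arm and no such reason in the other. First-attempters in the two arms could then differ in make-up for reasons other than chance.

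The second is the care plan. Its recommendations and prescriptions are part of usual care, and the Statistical method section intends to take concomitant drugs into consideration so that they do not bias the results. A record made after allocation is a weaker basis for that.

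**Working it through.** The plan gives no figure on this point and no arithmetic applies. The check is to set the passages side by side and ask what is already fixed when the envelope is opened.

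**Step 1. Order of events.** Procedure section: criteria verified, patient informed, consent obtained, patient randomised, data collected. The word that marks time is attached to randomisation. The sentence on data collection has none, so its place after allocation is read from the order of the sentences. No other section puts the recording earlier.

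**Step 2. Who knows the arm.** The Randomisation section has the investigator allocate by envelope and know the result. The Procedure section speaks of a physician. I assume that this is the investigator or a colleague with the same knowledge; the article does not separate the two roles or keep the physician blind.

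**Step 3. What eligibility already fixes.** The exclusion needs an attempt count over the past three years, and criteria are verified before randomisation. Against what the intervention needs to know, this gives:

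| Attempts before the index one, past three years | Eligible on this criterion | First-attempt status settled by the check? |
|---|---|---|
| At the exclusion limit | No | Not relevant |
| At least one, below the limit | Yes | Yes: not a first attempt |
| None | Yes | No: a first attempt, or an earlier one more than three years ago |

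The last row is the open one. A patient whose only earlier attempt was five years ago passes the eligibility check exactly as a first-attempter does, yet the two belong to different branches of the algorithm. The check also requires only that the count be below the limit, and the article does not say that an exact count is written down at that stage.

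**Step 4. Where attempt history is used.**

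- Choice between card and call, ALGOS arm only (Crisis card and Telephone contact sections).
- Possible rebalancing after 450 inclusions (Randomisation section). An imbalance seen there could partly reflect recording that differs by arm.
- Response profiles by first-attempt status (last secondary objective, Aims and Hypothesis section).
- Any model that includes it. The Statistical method section plans logistic regression for predictors of repetition but does not list covariates.

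**Step 5. The care plan.** The Procedure section calls it a plan defined in the ED and collects only its outline, so for most patients the physician would be copying an existing plan. A patient included at discharge, up to 7 days after the attempt, would normally have one. A patient included during the ED stay may not. One listed item, whether someone accompanies the patient at discharge, may not be known at that time.

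**Step 6. Effect on the main comparison.** The primary endpoint counts repeaters at 6 months in each randomised group. Misclassifying attempt history does not move anyone between groups, so the unadjusted comparison of all randomised patients remains a comparison of randomised groups. Sending an ALGOS patient down the wrong branch changes what was delivered, not who is compared.

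**The case against.** The strongest reply is that this is sentence order in a condensed article, not a stated procedure. The data sentence can be read as a list of what the physician gathers at inclusion. A three-year count must exist before allocation, and the care plan is described as already made. All of this is fair. It means that the article does not show the form being completed after the envelope is opened; it describes that order and states no safeguard against it. The reply does not remove the gap at first-attempt status (last row of the table) or the position of patients included during the ED stay.

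A reader might infer three stronger things, none of which the documents support.

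- *That the care plan is decided with the arm known, so that the primary comparison is biased.* The text describes recording a plan made in the ED. It may still be open only for patients included there. Closer care given to controls later would come from the investigator's knowledge of the arm, which the article discloses, and not from when the form is completed; an earlier form would not prevent it. The documents give no figure for such an effect.
- *That investigators can predict the next envelope.* That would need a block size, blocking within centre and tracking of past allocations. The article states neither block size nor blocking within centre. Details of numbering, sealing and block length are commonly left to the full protocol.
- *That centralised randomisation and envelopes contradict each other.* A central list with envelopes held at the sites fits both descriptions.

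**Conclusion.** The point holds as a weakness in the described sequence. As written, attempt history and the care plan outline are recorded after randomisation by staff who may know the arm, and the eligibility check does not settle first-attempt status for patients with no earlier attempt in the past three years.

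What is exposed is delivery of the right component in the ALGOS arm, first-attempter subgroup results, the possible rebalancing, and any adjustment using these variables. The comparison of all randomised patients is not biased by this alone.

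No numerical size can be given: the article does not say how many patients have only older attempts, nor how many are included during the ED stay. The conclusion rests on two assumptions: that the order of the sentences is the order of the work, and that the recording physician knows the allocation. If the full protocol places the recording before allocation, only a correction of wording remains. This is a cheap improvement, not a fault that undermines the trial.

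**What to change.** Reorder the Procedure section so that the following are recorded and signed before the envelope is opened:

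- number of previous attempts, with an explicit lifetime entry for whether the index attempt is the first;
- socio-demographic data;
- the ED care plan as it stands at that moment, with any item not yet known marked as such.

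Later changes to the care plan should be entered separately and dated, so that the entry made before allocation stays intact for subgroup and adjusted analyses. The choice between card and call, the possible rebalancing and the response profiles should all use the signed entry.

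The cost is a few minutes per inclusion and a change in the order of one form. Sample size, the interventions and the endpoints are unaffected. For patients included during the ED stay, the early record will sometimes be incomplete; that is the price of fixing it before allocation. The change does not control care given afterwards by staff who know the arm, and should not be presented as doing so.

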## Intervention

### For ALGOS patients group

#### 1. Delivery of a «Crisis Card»

All participants surviving a first SA receive a «crisis card» with the emergency phone numbers of the centre where they are included. This card is inspired from the proposed "crisis card" of Evans'team: format of a credit card, green (the colour of hope), plastified, identical for the whole territory containing the logos of suicide prevention organizations (with websites addresses) and personalized with the phone number of the 24 h care permanence of the concerned centre (see Figure 1) [10].

**Figure 1 F1:**
[figure not shown]
**Example of crisis card**.

#### 2. Telephone contact

As regards the other patients (not first-attempters), a phone call is conducted between the 10th and 21st day after the SA. The trained psychologist ensures as possible the identity of the patient and gets only addressed to the patient himself. The phone call is done on behalf of the initial unit where the patient was included. The telephone contact presents a part of a psychological support, which is based mainly on empathy, reassurance, explanation and suggestion. The aim of this interview is to verify the adequacy of responses to the existing healthcare, and otherwise to encourage and advise the patient to make new contacts. Three types of phone calls are distinguished according to the time of collecting responses [7]:

- Ordinary call (the most common): the treatment plan is still actual and valid, or the crisis situation that the participant lived improves. In this case, no help or advice seems necessary.

- Participant in difficulty or non compliant: the treatment plan is no longer valid or not followed, unwillingness exists, or the subject is in psychological difficulty: a new treatment plan is eventually suggested, which is already tried during the phone call. In addition, the concerned contact centre will send "postcards" during the following five months.

- Identification of participant at high risk of suicide: the patient is still victim of intrusive suicidal thoughts, asking or not for help. The investigator asks the patient to go to the ED where he was originally treated, to be received by a doctor informed by the concerned contact centre. In case of refusal by the participant, his general practitioner or the mobile emergency medical teams "SAMU/Centre 15" are called. The concerned contact centre will send "postcards" during the following five months.

Telephone contact will be abandoned, if unsuccessful after at least 3 call attempts on 3 different days at 3 different daytimes, and sending "postcards" will be scheduled for the next 5 months.

In all cases, a report of the telephone calls (or if the participant is lost of contact, the information that we have failed to call him) is sent to the general practitioner and eventually to the psychiatrist treating patient.

